#### Intervention description.

All participants of the IG and the CG will receive an educational session explaining the intervention details and an initial training session on how to perform exercises along with advices on proper position and ergonomics to be applied during daily work (***i.e.,*** ensure your workstation setup promotes good posture, with the monitor at eye level and the keyboard and mouse positioned close to your body; take regular breaks from sitting, standing, or staring at screens to stretch and move around). Participants will be instructed to carry out exercises at the same time daily, three to five days per week for 12 weeks.

For the CG, the rehabilitation program is delivered on a paper sheet containing pictures of exercises with a written explanation in French language with the number of sets and repetitions. Participants assigned to the IG will use the smartphone app. The latter includes the rehabilitation program with a detailed explanation in French language with the number of sets and repetitions.

Based on the findings of some papers [13,14], which focused on the effectiveness of exercise interventions for office workers with NP, we selected sets of self-exercise program with detailed explanation suitable for this population (Table 1).

**Table 1 pone.0329863.t001:** Neck self-exercises program.

Items	Description
** *Stretching exercises* **	.***Neck flexion stretch***: Sit tall in a chair; gently lower your chin towards your chest until you feel a stretch in the back of your neck. Hold for 30 seconds and repeat 3 times. .**Neck extension stretch**: Sit tall in a chair; gently tilt your head backward, looking towards the ceiling until you feel a stretch in the front of your neck. Hold for 30 seconds and repeat 3 times. .**Side neck stretch**: Sit tall in a chair; gently tilt your head towards one shoulder until you feel a stretch on the opposite side of your neck. Hold for 30 seconds and repeat on the other side. Repeat 3 times on each side

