### Description of the developed smartphone app

The smartphone app is designed using Android Studio and Flutter. It integrates advanced features, including an intuitive interface and an easy-to-use solution for all users (***i.e.,*** patients and healthcare professionals). Each participant in the IG will receive a code and password to log into the app and to register some general information such as age and sex. All assigned authentications will be recorded in a database created by Firebase. The app features several integrated modules:

(i) Basic information about NP and ergonomic advice on proper neck position during daily work,(ii) Series of evaluation questions including pain assessment (PI-NRS) and the impact of NP on participant’s daily functioning,(iii) Appropriate sets of exercises with videos and instructions,(iv) Daily reminder feature to prompt users to engage in their prescribed exercises consistently, and(v) Evaluation report providing feedback on user’s state and tracking their adherence.

To record participants’ engagement with the program, adherence will be monitored using a user activation tracking system assessing the frequency and duration of app use. The application is linked to the Cloud and Firebase tool enabling the therapist to visualize participants’ results in a graphical form. Exercises included are automatically adapted at each use of the app according to the participant’s condition and evolution. Indeed, the app is designed to analyze the data collected before each use from the evaluation questions based on an AI algorithm and to provide personalized exercise recommendations. To monitor and ensure participant engagement, app usage analytics will be utilized to track interaction patterns and identify any drop-offs in usage. Participants will also have access to technical support to troubleshoot any issues with the app, ensuring minimal disruption. Additionally, scheduled check-ins with participants will be conducted to address potential barriers to engagement and encourage continued adherence to the intervention protocol.

The diagram block (Fig 3) illustrates the app, which is composed of distinct therapist and participant interfaces.

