### Outcomes

The main outcome measure is pain intensity, evaluated according to the PI-NRS [28–30]. The latter is a commonly used tool to measure a person’s pain intensity [28–30]. It is simple, quick, and widely accepted in both clinical and research settings [28–30]. Participants will be asked to indicate their current level of pain on a line from 0 (no pain) to 10 (unbearable pain) [28–30].

Secondary outcome measures are function (***i.e.,*** neck disability index (NDI)), QoL and participants’ adherence to self-exercises. The French validated version of the NDI will be used to assess the impact of NP on individual’s daily functioning [31]. The scale consists of a set of questions addressing various aspects of NP and its influence on activities such as personal care, lifting, reading, working, and recreation. Participants will be asked to rate their level of disability or limitation on a scale for each activity. The total score provides a quantitative measure of the perceived disability associated with NP, with higher scores indicating greater impairment [32]. The French validated version of the short form 12 (SF-12) will be used to measure health-related QoL. The SF-12 is a shorter version of the short form 36, which assesses an individual’s physical and mental well-being. The SF-12 is often utilized in health research, clinical practice, and population health studies [33,34]. Adherence will be measured via two methods. First, it will be evaluated using a frequency-based response scale (***i.e.,*** never, seldom, often, almost always, and always) adapted from the adherence scale of Sluijs et al. [35]. Adherence will then be treated as a dichotomous variable (***i.e.,*** adherent or not adherent), participants who will report “always” or “almost always” will be considered adherent [21]. Second, adherence will be measured based on the frequency of exercise sessions completed. Participants who engage in exercises three or more times per week will be categorized as demonstrating “full adherence” whereas those who exercise twice per week or less will be considered to exhibit “partial adherence”. These combined methods ensure a comprehensive evaluation of adherence, capturing both self-reported behavior and objective frequency of exercise.

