### Methods: Data collection, management, and analysis

#### Plans for assessment and collection of outcomes.

Evaluations will be made at baseline, at the end of the intervention period (fourth week), and at 12 weeks follow up. All evaluations will be performed digitally through a questionnaire where participants will be invited to self-report their level of pain (PI-NRS), their functional disability (NDI), their QoL (SF-12), and to rate their adherence to exercises. At the baseline education session, questionnaires and evaluation tools will be explained to participants to resolve any doubt while answering.

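### The sessions-per-week adherence measure is called objective, but the only objective source described is app-use tracking in the intervention arm; the protocol should name one source common to both arms

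*Protocol article*

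**What the plan says.** The Outcomes section of the protocol article lists adherence among the secondary outcomes and measures it in two ways.

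- First, "it will be evaluated using a frequency-based response scale" with five levels; the top two count as adherent.
- "Second, adherence will be measured based on the frequency of exercise sessions completed": three or more sessions a week is full adherence, two or fewer is partial adherence.

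The section then concludes: "These combined methods ensure a comprehensive evaluation of adherence, capturing both self-reported behavior and objective frequency of exercise". It limits this claim to neither arm and names no data source for the session count.

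Three other sections bear on where that count could come from.

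- Description of the developed smartphone app: "adherence will be monitored using a user activation tracking system assessing the frequency and duration of app use". Access is confined to one arm: "Each participant in the IG will receive a code and password to log into the app".
- Intervention description: "For the CG, the rehabilitation program is delivered on a paper sheet containing pictures of exercises". No log, diary or device is described for these participants. The daily notification that both arms receive (Strategies to improve adherence to interventions) is a prompt and records nothing.
- Plans for assessment and collection of outcomes: "All evaluations will be performed digitally through a questionnaire where participants will be invited to self-report" their outcomes, and adherence is among the items they rate. No arm is excepted.

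The Statistical methods section includes adherence among the outcomes whose between-group differences will be estimated.

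**The concern.** A between-group contrast is interpretable only if the outcome is measured the same way in both arms. The protocol claims an objective session frequency and describes an automatic record that it says monitors adherence, but only app users can generate that record. A statistician following the Outcomes and app sections together could reasonably take session frequency from the log in one arm and from questionnaires in the other. The estimated difference in full adherence would then combine any real difference with the difference between log and self-report.

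The log also does not measure the quantity defined in the Outcomes section. It captures how often and how long the app is used. A participant who has learned the routine and exercises without opening the app is missed; one who opens the app and does not exercise is counted.

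The Objective section anticipates that the app will address the problem of adherence. A difference in full adherence, or the lack of one, could be put forward as evidence on that expectation when it partly reflects the measuring instrument.

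**Working it through.** **Step 1. Sources of session frequency by arm.** The plan states no figure for adherence, so there is none to reproduce. The sections compare as follows.

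| | App arm | Paper arm |
|---|---|---|
| Automatic record | App-use tracking | None described |
| Questionnaire, self-report | Yes | Yes |
| Five-level adherence scale | Yes, self-report | Yes, self-report |
| Source named for sessions per week | No | No |

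Two readings are open:

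- *The log supplies the count in the app arm.* Nothing but self-report is described for the paper arm, so method and treatment are confounded.
- *The questionnaire supplies the count in both arms.* The method is common, but nothing in the comparison is objective, and the Outcomes section is wrong to say so.

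Neither reading gives an objective measure in both arms.

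**Step 2. Illustrative size under the first reading.** All error rates here are assumptions; none comes from the documents. Let *p* be true full adherence, equal in both arms; *m* the share of truly adherent app users whose exercise the log misses; and *f* the share of non-adherent controls who report three or more sessions.

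- Apparent rate, app arm: *p*(1 − *m*)
- Apparent rate, paper arm: *p* + (1 − *p*)*f*

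Rejection rates come from exact binomial enumeration of a two-sided 5% pooled z-test of two proportions with 25 per arm (the arm size given under Sample size).

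| *p* | *m* | *f* | App arm | Paper arm | Difference (points) | Rejection rate |
|---|---|---|---|---|---|---|
| 0.5 | 0 | 0 | 0.50 | 0.50 | 0 | 6.5% |
| 0.5 | 0 | 0.2 | 0.50 | 0.60 | −10 | 13% |
| 0.5 | 0 | 0.4 | 0.50 | 0.70 | −20 | 33% |
| 0.5 | 0.1 | 0.2 | 0.45 | 0.60 | −15 | 22% |
| 0.5 | 0.2 | 0.4 | 0.40 | 0.70 | −30 | 62% |
| 0.4 | 0 | 0.2 | 0.40 | 0.52 | −12 | 16% |
| 0.6 | 0 | 0.2 | 0.60 | 0.68 | −8 | 10% |

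For example, in the second row the paper arm is 0.5 + 0.5 × 0.2 = 0.60, so the difference is 0.50 − 0.60 = −0.10. The first row is the reference: with a common, error-free method this test rejects 6.5% of the time at this sample size, slightly above its nominal 5%.

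**Step 3. Direction.** Suppose instead that self-report is accurate and the log counts 20% of non-adherent app users as fully adherent because they open the app. The app arm then shows 0.5 + 0.5 × 0.2 = 0.60 against 0.50, a spurious 10 points in favour of the app. The sign depends on which error dominates, and the documents do not allow that to be judged.

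**The case against.** The strongest reply is that the protocol never says the two sources will be mixed. The Outcomes section names no source for session frequency. The app section does not say the log feeds the full/partial classification; it also describes tracking as a way to follow engagement and detect falling use. The outcome-collection section points to one questionnaire for all participants. On that reading the recommended comparison is close to what is already planned, and the fault is one unsupported word. A condensed article may also leave the item wording, or a control-arm diary, to the full protocol.

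Much of this stands. A reader might infer that the adherence comparison as a whole does mix logs with self-report and is biased, perhaps against the app. The text does not support that. The mixing is an inference; only the second of two measures is exposed to it; and the size and sign rest on assumed error rates. A reader might also add that zero sessions is classed as partial adherence. That label is awkward, but it does not change who counts as fully adherent and so does not affect the binary contrast.

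The reply does not remove the point. The app section says in terms that adherence will be monitored by tracking, and the Outcomes section makes a positive claim of objectivity without limiting it to an arm. This is a statement that the described procedures cannot meet on either reading, which is different from a detail left out for brevity.

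**Conclusion.** The point holds as a conditional one. The app, Outcomes and outcome-collection sections do not agree on where session frequency comes from, and no objective measure is described for the paper arm. If app logs are used for the intervention group, as the app section indicates, the frequency contrast is confounded with measurement method in an unknown direction. If both arms self-report, that confounding is absent and the claim of objectivity is mistaken.

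The 8 to 30 point differences and 10% to 62% rejection rates tabulated above show what the first reading could produce under the assumed error rates; they are not estimates for this trial. The consequence is limited to one of two measures of one secondary outcome. The five-level scale gives a comparison by the same method in both arms, and the primary pain outcome is untouched. The protocol should still be corrected, because the source can be fixed cheaply before data collection, and bias of unknown sign cannot be reliably removed at analysis.

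**What to change.** Reconcile the three sections as follows.

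- State in the Outcomes section that the between-group frequency comparison uses one self-reported sessions-per-week item, with the same wording and recall period in both arms, collected in the week 4 and week 12 questionnaires.
- State in the app section that tracking data are reported descriptively for the intervention group only, including their agreement with self-reported frequency, and do not enter the between-group comparison.
- Drop the word objective from the description of the comparative measure.

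The cost is at most one questionnaire item in a digital form already planned, plus wording changes. The downside is that the comparison then rests on self-report by participants who know their allocation (Blinding section), and app users also receive feedback on their own adherence. Some differential reporting may therefore remain and should be acknowledged as a limitation. The log-versus-report agreement in the app arm would give some indication of reporting error there, but none for the paper arm.

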### Participant timeline

Participants will be assessed at 4 and 12 weeks. A schematic diagram for participants’ timeline is shown in Fig 1.

### Sample size

The null hypothesis [36] was H_0_: m_1_ = m_2_, and the alternative hypothesis was H_a_: m_1_ = m_2_ + d, where “***d***” is the difference between two means and n_1_ and n_2_ are the sample sizes for the interventional and control groups, such N = n_1 _+ n_2_. The sample size was estimated using the following predictive equation [36]: $\text{n}\;=\;[\text{2}\;{\text{s}}^{\text{2}}\;{\left({\text{Z}}_{\text{1}-\alpha /\text{2}}\;+\;{\text{Z}}_{\text{1}-\beta }\right)}^{\text{2}}]/{\text{d}}^{\text{2}}$, where

“***n***” is the number of participants;“***Z***_***1-α/2***_” is the normal deviate at a level of significance (type I error at 2-sided = 1.96 at 5% level of significance);“***Z***_***1-β***_” is the normal deviate at 1-β% power with β% of type II error (0.84 at 80% statistical power);“***d***” is the expected difference between average changes of PI-NRS from two groups; and“***s***” is the common variance (standard deviation) of PI-NRS means of two groups. “***s***” was calculated according to the following formula [36]: ${\text{s}}^{\text{2}}\;=\;[({\text{n}}_{\text{1}}-\text{1x}\;{{\text{s}}_{\text{1}}}^{\text{2}}\;+\;({\text{n}}_{\text{2}}-\text{1})\;\text{x}\;{{\text{s}}_{\text{2}}}^{\text{2}}]/({\text{n}}_{\text{1}}+{\text{n}}_{\text{2}}-\text{2})$ .

“***d***” and “***s***” values were obtained from a previous South Korean study [37] including 34 patients (17 in the IG and 17 in the CG). The patients in the IG performed exercises using a video-based app system, whereas those in the CG performed exercises using an image- and text- based printout [37]. In-home training was implemented for six weeks in both groups [37]. The NP intensity was measured before and after the intervention via the PI-NRS. Kim and Shin [37] reported that within both groups, the PI-NRS improved significantly after the intervention. At the end of the intervention, PI-NRS’ changes (expressed as means ± standard deviation) for the IG and CG were 2.23 ± 1.85 and 1.65 ± 1.26, respectively (“***d***” is therefore equal to 0.58 (0.58 = 2.23 - 1.65). Based on the aforementioned study [37], where n_1_ = 17, n_2_ = 17, s_1_ = 1.85, s_2_ = 1.26, “***s***^***2***^” is equal to 2.51 [2.51= [(17-1) x 1.85^2^ + (17-1) x 1.26^2^]/(17 + 17-2)].

The injection of the aforementioned data in the predictive equation gave a sample size of 117 participants. However, since our study involves a finite population (***i.e.,*** a population with a limited number of participant), a correction was applied to the sample size [36]. The number of participants to be included after correction is given by the formula n’ = (N x n)/(N + n), where “ ***n’*** ” represents the corrected sample size, “ ***N*** ” is the size of the finite population (which is 70 office workers in our study), and “ ***n*** ” is the sample size calculated from the standard formula (n = 117). Therefore, the corrected minimum sample size (***n’***) is equal to 44 participants [44 = (70 x 117)/(70 + 117)]. Assuming a 10% absence during the end of the intervention period, 50 participants (25 in each group) were determined to be the amended sample size [50 = 44/ (1–0.1)].

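### The sample size formula gives 117 per group, but the protocol uses 117 as the total for both groups and so halves its own uncorrected requirement

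*Protocol article*

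**What the plan says.** All of this is in the Sample size section of the protocol article.

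- It sets up a comparison of two means, names n₁ and n₂ as the group sizes and N as their sum, and gives n = 2s²(Z₁₋α/₂ + Z₁₋β)²/d². It says only that n "is the number of participants", not whether that means each group or both.
- The error rates are "type I error at 2-sided = 1.96 at 5% level of significance" and "0.84 at 80% statistical power".
- The expected difference d "is therefore equal to 0.58 (0.58 = 2.23 - 1.65"). It comes from an earlier study of a video-based app against a printout, "where n_1_ = 17, n_2_ = 17, s_1_ = 1.85, s_2_ = 1.26". From these the pooled variance "is equal to 2.51 [2.51= [(17-1) x 1.85^2^ + (17-1) x 1.26^2^]/(17 + 17-2")].
- The result is then stated: "The injection of the aforementioned data in the predictive equation gave a sample size of 117 participants".
- The figure of 117 is combined with the workforce of 70 in a finite-population formula to give 44. After allowance for 10% loss, "50 participants (25 in each group) were determined to be the amended sample size".

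Nowhere is 117 doubled or described as a per-group number.

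**The concern.** In a two-arm comparison with equal groups, the formula with the factor 2 returns the number in one arm. The last step of the protocol's chain, which splits 50 into two groups of 25, shows that 117 and then 44 were handled as totals for both arms. If so, the starting figure is half of what the stated inputs require, before any finite-population correction is applied.

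Two things are at stake. First, this section is the only justification for the size of a trial that the abstract describes as a superiority trial, and a reader will take it to deliver 80% power. A null result could then be read as evidence of no difference when the trial had little chance of detecting the difference it was planned for. Second, the finite-population correction is itself open to challenge. If it were dropped and nothing else changed, 117 in total would look like the properly powered size, and it is not. Anyone who reused the calculation for a larger trial would plan half the number needed.

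**Working it through.** **Inputs (all from the Sample size section).** Z₁₋α/₂ = 1.96; Z₁₋β = 0.84; d = 2.23 − 1.65 = 0.58; s₁ = 1.85, s₂ = 1.26, n₁ = n₂ = 17. Allocation is 1:1 (Allocation section).

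**1. Pooled variance.** s² = (16 × 1.85² + 16 × 1.26²)/32 = 2.505, stated as 2.51. It reproduces.

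**2. The protocol's 117.** n = 2 × 2.51 × (1.96 + 0.84)²/0.58² = 2 × 2.51 × 7.84/0.3364 = 116.99, so 117. It reproduces.

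**3. What n counts.** With n participants in each arm and common variance s², the variance of the difference in means is s²/n + s²/n = 2s²/n. Setting d = (1.96 + 0.84) × √(2s²/n) and solving for n gives n = 2s²(1.96 + 0.84)²/d², which is the protocol's formula. So n is the number per arm. The total for both arms is 4s²(1.96 + 0.84)²/d² = 4 × 2.51 × 7.84/0.3364 = 233.99, so 234.

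**4. Could 117 be a total under other settings?** Totals for the same d and s², with unrounded Z values:

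| Setting | Per arm | Total |
|---|---|---|
| Two-sided 5%, 80% power | 118 | 236 |
| One-sided 5%, 80% power | 93 | 186 |
| Two-sided 5%, 90% power | 157 | 314 |
| One-sided 5%, 90% power | 128 | 256 |

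None of these gives 117 as a total.

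**5. How the protocol uses it.** 70 × 117/(70 + 117) = 43.8, so 44; 44/0.9 = 48.9, so 49, rounded to an even 50; 50/2 = 25 per group. On a per-group reading, 44 would have been the size of each group before loss.

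**6. Requirement without the finite-population correction.** 117 per arm × 2 = 234 completers. With 10% loss, 117/0.9 = 130 per arm, so 260 randomised.

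**7. Power at d = 0.58, s² = 2.51** (two-sample t test, two-sided 5%, noncentral t):

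| Completers per arm | Total | Power |
|---|---|---|
| 117 | 234 | 0.796 |
| 58 | 116 | 0.498 |
| 25 | 50 | 0.245 |
| 22 | 44 | 0.220 |

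So 117 in total, about 58 to 59 per arm, gives about 50% power.

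**8. Precision at the planned size.** The standard error of the difference is √(2 × 2.51/n): 0.448 at 25 per arm and 0.478 at 22 per arm. The 95% confidence interval half-width is about 0.90 and 0.96 points respectively. The difference detectable with 80% power is 2.8 × 0.448 = 1.25 points at 25 per arm and 2.8 × 0.478 = 1.34 points at 22 per arm, against a planned d of 0.58.

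**9. Separating the two steps.** Treating 117 as a total takes 234 to 117, a halving. The finite-population correction then takes 117 to 44, a further cut of 1 − 44/117 = 62%. Together they leave 44/234 = 19% of the requirement. If the correction were kept and only this error repaired, 70 × 234/(70 + 234) = 53.9, so 54, and 54/0.9 = 60: the planned total would be 60 instead of 50.

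**The case against.** The arithmetic is not in dispute. The best case against giving the point much weight has four parts.

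- **The larger loss comes from elsewhere.** The finite-population correction removes more than the halving does, and within the protocol's own method this error moves the target only from 50 to 60. That is correct. The 19% figure should be read as the joint effect of both steps; this one alone accounts for the factor of two.
- **Nobody proposes a trial of 117**, so its 50% power describes a design that is not planned. This is fair as far as it goes. But 117 is presented as what 80% power requires, and it is the number that surfaces as soon as the correction is questioned.
- **The quoted sentence is not false in itself**, since the equation does return 117, and n is loosely labelled rather than called a total. That stands for the sentence alone. The later split into 25 per group settles how the figure was used.
- **The power figures assume a t test on change scores**, while the Statistical methods section plans a repeated-measures mixed model with adjustment for baseline imbalance. The figures are therefore approximate for the planned analysis. They do, however, match the basis on which the protocol sized the trial, and a different analysis does not turn a per-group formula into a total.

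A further caution bears on the remedy. The setting supplies a ceiling of 70 workers before eligibility is applied, and the figure of 50 comes from the calculation rather than from a count of eligible staff.

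**Conclusion.** The error is real and must be corrected. On the protocol's own inputs, 117 is the number per group. The uncorrected requirement is 234 completers, or 260 randomised with 10% loss, and the protocol states it at half that size. Taken as a total, 117 gives about 50% power rather than 80%. At the planned size, power for d = 0.58 is about 0.25 with 25 per arm and 0.22 with 22 completers per arm; most of that shortfall is due to the finite-population correction. The conclusion that n is per group follows from the formula and needs no assumption beyond equal groups and a common variance. The power figures also assume d = 0.58, s² = 2.51 and a two-sided 5% t test on the change in pain score.

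**What to change.** In the Sample size section:

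1. Define n as the number of participants per group.
2. State that the formula gives 117 per group, 234 in total, and 260 randomised with 10% loss.
3. State that this cannot be reached with a workforce of 70, and that the trial is limited to about 50 by its setting. Give the feasibility grounds for 50 (the expected number of eligible and willing workers), rather than presenting it as the output of a power calculation.
4. Report what that size provides: power of about 0.25 at 25 per arm and 0.22 at 22 completers per arm for d = 0.58, and a 95% confidence interval half-width of about 0.9 to 1.0 points.

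The finite-population correction needs its own justification or removal. Doubling 117 while keeping it would only move the target to 60 and would not restore 80% power.

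The cost is a change of wording and corrected figures, with review by the ethics committee as the protocol requires for amendments. No extra participants are needed, and allocation, outcomes and analysis are unchanged.
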